## Abstract

**Background:**

A positive, prosocial classroom climate is associated with improved social competence and academic achievement, as well as with decreased internalizing problems and antisocial behavior in children. It is expected that motivation to behave prosocially is needed to achieve a prosocial climate in the classroom, and that such motivation can be enhanced through three components of self-determination theory (SDT): competence, relatedness, and autonomy. The goal of this protocol is to describe the design of a study aiming to evaluate the effectiveness of a classroom-based program based on SDT components promoting a prosocial classroom climate.

**Methods:**

A cluster randomized controlled trial (RCT) will be conducted to examine the effectiveness of the classroom-based program Meaningful Roles, aiming to improve prosocial classroom climate through increasing children’s intrinsic prosocial motivation, stimulated by increasing social autonomy, social competence, and social relatedness. A multi-informant (i.e., children, teachers, and school leaders) and multi-method (i.e., questionnaires and focus groups) approach will be used to assess primary outcomes (i.e., prosocial behavior, intrinsic (prosocial) motivation, social autonomy, social competence, and social relatedness) and secondary outcomes (i.e., school wellbeing, social position, bullying, victimization, and civic skills), as well as moderators (i.e., working elements, child, teacher, school, and program characteristics, and program integrity).

**Discussion:**

The current study will provide information on the effectiveness of a classroom-based program promoting a prosocial classroom climate. It is of crucial importance that the school environment can provide a positive, prosocial classroom climate in which children feel safe and can achieve optimal social and academic competence and wellbeing.

**Trial registration:**

ClinicalTrials (NCT05891067).

## Background

A positive, prosocial classroom climate is crucial in promoting children’s school and psychological wellbeing, as well as in optimizing an effective learning environment [1, 2]. Previous research demonstrated that bullying perpetration and being victimized are less common in classrooms with a positive, caring, and supportive climate [3, 4]. Although classroom climate can be conceptualized in many ways, we focus on the emotional classroom climate domain as it is considered to be most vital to other aspects of classroom climate [2]. Positive emotional classroom climate is characterized by a prosocial behavior classroom norm (both injunctive and descriptive), high levels of collaboration, high quality of teacher and peer interactions, as well as low level of conflicts [1, 5, 6].

What is needed to create a prosocial classroom climate? According to the self-determination theory (SDT), behaviors are only encouraged when children experience intrinsic motivation for these behaviors. Moreover, such motivation (and behavior) is stimulated when children perceive that their environment fulfills their three fundamental needs: for autonomy, competence and relatedness (i.e., how autonomous, competent and related they feel within a particular context) [7, 8]. Enhancement of the needs of autonomy (the feeling of being independent, being able to decide for oneself), competence (confidence in one’s abilities) and relatedness (sense of belonging, trust in others) enables, for instance, greater empathy toward others, better coping with conflict, internalization of a prosocial behavior classroom norm, and a caring classroom environment [8]. Consequently, this increases children’s motivation to behave prosocially [8]. According to the goal-framing theory, the prevailing group norm influences what behavior is supported and reinforced and what behavior is not [9]. To ensure that prosocial behavior becomes a persistent basis of the classroom climate, prosocial behavior should become the social norm in the classroom (i.e., normative goal). Maintaining such a norm occurs through perceiving prosocial attitudes and support by others, such as peers and teachers [9]. The current protocol describes a study that examines the effectiveness of a classroom-based program promoting a prosocial classroom climate in primary schools, stimulated by increasing STD components and prosocial intrinsic behavior (i.e., Dutch adaptation of Meaningful Roles [SterkWerk]).

The program is based on Meaningful Roles, an antibullying intervention program offering bullies prosocial alternatives for their behavior (by increasing autonomy and relatedness) [10]. Results demonstrated reduced aggressive and problem behaviors at one school (e.g., fewer fights, detentions) [10], suggesting the positive effects of promoting prosocial behavior. Other research also showed the effectiveness of such intervention programs. Prosocial behavior interventions were found to be effective in promoting prosocial behavior in children and adolescent samples [11–13], especially for programs that were designed to increase social competence instead of preventing problem behavior [11]. Additionally, one single-school pilot study demonstrated that a one-year classroom climate intervention (focused on mindfulness, prosocial behavior, self-curiosity, and self-acceptance) improved the classroom environment for both teachers and students [14]. Furthermore, meta-analyses demonstrated that classroom-based social and emotional learning interventions had small to large effects on improving social and emotional skills, positive attitudes, positive social behavior, and indicators of wellbeing (e.g., fewer conduct problems, less emotional distress) in children and adolescents [15–18]. In addition, recent meta-analyses showed that anti-bullying programs were effective in decreasing school-bullying perpetration and victimization in children and adolescents [19, 20], revealing larger effects for specific components (e.g., whole-school approach, classroom rules, information for parents, informal peer involvement) [21] and specific groups (i.e., younger and more heavily victimized participants) [20]. Additionally, a recent meta-analysis in youth and adult samples demonstrated that SDT-informed intervention programs were associated with positive changes in SDT constructs (i.e., autonomy, competence and relatedness), as well as positive changes in physical and psychological health [22].

In sum, there is both theoretical evidence and there are empirical suggestions that prosocial classroom climate can be improved through enhancing children’s motivation to behave prosocially by targeting SDT components. Moreover, empirical research on the effectiveness of school- or classroom-based programs in primary school demonstrated promising results for improving prosocial classroom climate, increasing prosocial behavior and wellbeing, and decreasing antisocial behavior. However, previous knowledge can be extended in several ways. First, about half of the studies performed a (cluster) RCT, which means that in non-randomized studies there might be confounding factors. Second, most meta-analytic reviews and studies included several age cohorts (e.g., from kindergarten through high school, 4–18 years, from children to adults), not only primary school students, which precludes strong conclusions about this specific age group. Third, most studies were conducted in the United States, precluding conclusions about non-US samples. Hence, there is still not sufficient evidence for the effectiveness of classroom-based programs promoting prosocial behavior, specifically for programs based on STD components in primary school students. In addition, little is known about potential moderators of program effectiveness and the working elements of such programs.

Moderators are characteristics that are likely to affect the effectiveness of intervention programs, such as child, teacher, school, and program characteristics. Child characteristics that may affect program effectiveness include demographic characteristics (e.g., age, gender, ethnic identity background) and other factors (e.g., severity of problems or popularity of bullies at baseline). For instance, previous meta-analytic reviews showed that school-based interventions with older adolescents [23], a higher proportion of female adolescents [23, 24], and a greater proportion of ethnic minority youth [1, 23] were more effective. Furthermore, previous research showed larger program effects for children with more problem behavior before the start of the intervention [13, 25], while lower program effects were found for bullies with a high popularity at baseline [26].

Teacher characteristics that may affect program effectiveness include demographic characteristics (e.g., age, gender, ethnic identity) and other factors (e.g., years of experience). Previous meta-analytic studies examining the associations between student–teacher relationships and school adjustment showed that teachers’ gender and ethnicity moderated these associations [27, 28]. For example, female teachers might be able to better implement socioemotional programs, due to the traditional gender role of females as effective caretakers of child development [27]. In addition, experienced or older teachers might be more effective in implementing the program because they have more knowledge and have acquired greater skill. Indeed, previous research showed that teaching experience is positively related to student outcomes (e.g., achievement, motivation) [29]. School characteristics, such as years of experience with a social safety program (e.g., KiVa), school or class size, or location may moderate the effectiveness of the program. In line with this reasoning, if schools already have (much) experience with implementing social safety programs, it is likely that teachers at those schools may be more effective in implementing the current program. Furthermore, it is likely that teachers give students more individual attention in smaller classes, which might be important during classroom-based intervention programs and hence, may result in stronger effects. Program effectiveness may also differ based on location, as a previous meta-analysis examining the effectiveness of family interventions demonstrated smaller effects for urban settings compared to nonurban settings [30].

Program characteristics that may affect program effectiveness include program integrity and working elements. Program integrity, whether the intervention is implemented as originally planned, is important to report and to investigate as moderator of effectiveness, as it is necessary to draw conclusions about an intervention program. Negative or nonsignificant results might be due to incorrect program implementation, and not because of an ineffective program [31]. In addition, whether the working elements (i.e., meaningful roles, classroom meetings, and compliments) were implemented and how often may influence program effectiveness. Indeed, previous literature demonstrated that better implementation of school-based prevention programs is associated with more beneficial outcomes [15, 32].

### Current study

In sum, the current protocol describes a study that will be conducted to examine the effectiveness of a classroom-based program promoting a prosocial classroom climate (i.e., Meaningful Roles). Figure 1 presents the conceptual model of the research design. A cluster RCT will be performed to investigate if the program results in more prosocial classrooms (e.g., more prosocial behavior, more cooperation, less conflict). The program will be compared to a control condition. We will use a multi-informant (children, teachers, and school leaders) and multi-method (questionnaires and focus groups) design. As illustrated in Fig. 1, it is expected that Meaningful Roles will increase children’s social autonomy, social competence, and social relatedness, resulting in an increase in intrinsic (prosocial) motivation and a prosocial classroom climate (i.e., increased prosocial behavior, positive teacher attitudes, civic skills, and school wellbeing, and reduced bullying and bullying victimization). In addition, the second aim is to examine moderators of effectiveness. This is important because it is likely that Meaningful Roles is not equally effective across child, teacher, school, and program characteristics (i.e., program integrity). The final aims of this study are to evaluate the working elements of Meaningful Roles (i.e., meaningful roles, classroom meetings, and compliments) and to evaluate how the program is experienced by teachers and school leaders.

**Fig. 1 Fig1:**
[figure not shown]
Conceptual model of the research design

## Methods

### Design

A cluster RCT will be conducted. Schools will be randomized (stratified for number of participating classrooms) into the intervention condition in which the program starts immediately or into a control condition that receives the program one school year later (see Fig. 2), using an online randomization tool [33] in a 1:1 ratio. We will recruit a diverse sample of children from primary schools in the Netherlands.

**Fig. 2 Fig2:**
[figure not shown]
Flow chart of the research design

### Data collection

Online questionnaires assessing demographics (e.g., age, gender), primary outcomes (i.e., prosocial behavior, intrinsic prosocial motivation, social competence, social autonomy, and social relatedness) and secondary outcomes (i.e., school wellbeing, social position, and antisocial behavior) will be completed by children prior to the start (T1) of the program. Halfway through the program (T2) and after completion of the program in the intervention condition (T3), children complete questionnaires about program content (i.e., working elements) in addition to questionnaires assessing primary and secondary outcomes. Teachers complete questionnaires about demographics (e.g., age, years of experience), attitudes, and civic skills at T1 and questionnaires about attitudes, civic skills, program content (to assess program integrity), and program evaluation at T2 and T3. Additionally, one teacher from each school will participate in the focus groups (at T1, T2, and T3), to evaluate the implementation of the program (i.e., qualitative information). Table 1 presents an overview of the instruments at each assessment point.

**Table 1 Tab1:** Overview of the variables’ instruments and sources

Outcome	Variable name	Instrument	Time of measurement	Variable type	Source
Primary outcomes					
Prosocial behavior	Injunctive norm	Developed for this study	T1, T2, T3	Outcome	Child
	Prosocial behavior (individual)	Based on the Strengths and Difficulties questionnaire (SDQ), subscale prosocial behavior	T1, T2, T3	Outcome	Child
	Prosocial behavior (according to classmates)	Sociometric nominations	T1, T2, T3	Outcome	Child
	Cooperation in the classroom	Classroom Peer Context Questionnaire (CPCQ), subscale cooperation	T1, T2, T3	Outcome	Child
	Conflict in the classroom	Classroom Peer Context Questionnaire (CPCQ), subscale conflict	T1, T2, T3	Outcome	Child
Intrinsic (prosocial) motivation	Social goals	Developed for this study	T1, T2, T3	Outcome	Child
Social competence	Self-esteem	Developed for this study, based on de Rosenberg Self-Esteem Scale	T1, T2, T3	Outcome	Child
Social autonomy	Social autonomy and responsibility	Developed for this study, based on the School as a Caring Community Profile – II and Child Development Project [34]	T1, T2, T3	Outcome	Child
Social relatedness	Comfort and cohesion	Classroom Peer Context Questionnaire (CPCQ), subscale comfort and cohesion	T1, T2, T3	Outcome	Child
Secondary outcomes					
School wellbeing	School belonging and safety	School belonging and safety	T1, T2, T3	Outcome	Child
Social position	Injunctive norm (nominations)	Sociometric nominations	T1, T2, T3	Outcome	Child
Bullying and victimization	Bullying and victimization	Olweus Bully-Victim questionnaire and sociometric nominations	T1, T2, T3	Outcome	Child
Civic skills	Civic skills	Based on the Vragenlijst Burgerschap Meten	T1, T2, T3	Outcome / moderator	Teacher
Working elements					
	Meaningful roles	Developed for this study	T2, T3	Outcome / moderator	Child, teacher
	Classroom meetings	Developed for this study	T2, T3	Outcome / moderator	Child, teacher
	Compliments	Developed for this study	T2, T3	Outcome / moderator	Child, teacher
Moderators					
Child characteristics	Demographics	Developed for this study	T1	Moderator / covariate	Child
Teacher characteristics	Demographics	Developed for this study	T1	Moderator / covariate	Teacher
	Attitudes	Developed for this study	T1, T2, T3	Moderator / outcome	Teacher
Program characteristics	Program integrity	Developed for this study	T2, T3	Moderator / covariate	Teacher, school leader

The design of this study has been approved by the Ethical Committee of Utrecht University (number 23–0082) and is registered in the ClinicalTrials registry (NCT05891067).

### Study sample

We aim to include *N* = 42 schools to ensure there is enough power for the analyses (*N* = 21 schools for both the intervention and waitlist control condition). This sample size is sufficient to examine the effectiveness of Meaningful Roles and potential moderators, with a power of 0.80, an alpha of 0.05 and a medium effect size of 0.21 [18].

Participants are children from the upper grades of primary school (grades 5–8) in the Netherlands, their teachers (who will implement the program) and school leaders. The children will mostly be between 8 and 12 years old.

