
*Civic skills* will be assessed at all three timepoints, for teachers only. Specific questions were developed for this study, based on the questionnaire measuring citizenship ([Vragenlijst Burgerschap Meten]; [50]). Four domains will be assessed by asking teachers how the children in their class: 1) act democratically (e.g. “accept decisions made by the whole class (majority decisions)”, 2) act socially responsible (e.g., “stand up for each other”), 3) dealing with conflicts (e.g., “consider the other person in a conflict when looking for a solution”, and 4) dealing with differences (e.g., “are curious about what other children are good at (qualities)”. Higher scores reflect more (positive) civic skills in the classroom.

*Teacher attitudes* will be assessed at all three timepoints, with specific questionnaires developed for this study. Teachers are asked what they find important in their job as a teacher to stimulate, for example: “that children help each other in the classroom”. Higher scores reflect a positive attitude of stimulating prosocial behavior and STD components.

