There are several challenges in this study, such as the recruitment of a sufficient number of schools (and students) and the collaboration with multiple parties. First, it may be difficult to recruit sufficient schools with a diverse and representative sample of students and maintain the involvement of schools, teachers, students, and parents over the course of the study. Recruitment of schools may be difficult because we would preferably like schools to participate with all their upper classes (groups 5–8), which requires involvement and participation of multiple teachers (who all need to stand behind the program and research). To recruit schools, we will mainly try to contact schools who already have connections or collaborations with the research or implementation team (i.e., KiVa schools), making the first contact easier. These schools are located all throughout the Netherlands. As such, it is likely that diverse schools, with a diverse sample of students, will be represented in our study. Additionally, flyers will be distributed via mail and newsletters, and information meetings will be organized to give more information about the program and study participation.

Second, since participation of students requires active informed consent from their parents, it is crucial that all parents of participating classes are reached and are provided with clear information about study participation. Participating schools make sure that parents receive information about the project, and teachers will be responsible for contacting parents (e.g., face-to-face, mail, telephone). In order to make giving permission as easy as possible, parents can also give digital consent. Researchers and the contact person of the schools will be in constant contact to increase response rates. These precautions are expected to increase the likelihood of participation of students.

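### The 0.80 power statement is not limited to any outcome, yet two expected effects are measured in teachers only, where 42 schools probably give less than 0.80 at an effect of 0.21

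*Protocol article*

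**What the plan says.** The Study sample section sets the target at "42 schools to ensure there is enough power for the analyses", split as "21 schools for both the intervention and waitlist control condition", and states "This sample size is sufficient to examine the effectiveness of Meaningful Roles and potential moderators, with a power of 0.80". The figures are given once: "with a power of 0.80, an alpha of 0.05 and a medium effect size of 0.21". The section does not say which outcome they refer to, and it gives no number of respondents per school, ICC, sidedness or effect metric. The Design section randomises schools, "using an online randomization tool [33] in a 1:1 ratio".

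The Current study section describes the prosocial climate the program should bring about as "increased prosocial behavior, positive teacher attitudes, civic skills, and school wellbeing, and reduced bullying and bullying victimization". Two of those components have the teacher as their only source:

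- Civic skills is a secondary outcome that "will be assessed at all three timepoints, for teachers only". Each teacher rates how the children in the class behave, so one respondent gives one rating of a class.
- Teacher attitudes is described under the Secondary outcomes heading. Table 1 places it under Moderators, typed as both moderator and outcome.

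Every primary outcome in Table 1 is reported by children. The number of teachers is not stated. The Discussion says only that "we would preferably like schools to participate with all their upper classes (groups 5–8), which requires involvement and participation of multiple teachers".

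**The concern.** A sample of 42 schools supplies many children but few teachers. A power figure that may be attainable with dozens of children per school does not carry over to an outcome with a handful of respondents per school. The sentence covers effectiveness as a whole and even moderators, so a reader has no reason to exclude civic skills or teacher attitudes from it.

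What is at stake is how a null result is interpreted. Suppose the civic-skills comparison is not significant and the reader relies on the stated 0.80. The result then looks like adequately powered evidence of no effect on a hypothesised outcome. With about four teachers per school and a true difference of 0.21 SD in the teacher score, a non-significant result would be the more likely outcome.

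**Working it through.** **Inputs from the protocol.** 42 schools, 21 per arm, 1:1; alpha 0.05; effect 0.21; T1 score as covariate (Statistical analyses section).

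**Assumed, because the protocol does not give them.** Two-sided test; 0.21 is a standardised mean difference *d* in the score analysed; *m* = 2 to 8 teachers per school (four if each of groups 5 to 8 brings one class); ICC of 0 to 0.2 among teachers in a school; correlation *r* of 0 to 0.7 with the T1 score.

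**The stated figure first.** Without clustering, *d* = 0.21 needs 356 children per arm, which is 17 per school over 21 schools. With clustering and no baseline adjustment (normal approximation), 0.80 is reached for pairs such as 20 children per school with ICC 0.01, 40 with 0.035, 80 with 0.047 or 100 with 0.05. At ICC 0.10 and 80 children it is about 0.53. So 0.80 is attainable for child-reported outcomes, but it cannot be confirmed from what is stated.

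**Teacher-only outcomes.** The variance of the estimated difference in SD units is

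Var = (4/42) × (ICC + (1 − ICC)/*m*) × (1 − *r*²)

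Power comes from a noncentral *t* with 42 − 2 = 40 degrees of freedom and noncentrality 0.21/√Var.

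Example, *m* = 4, ICC 0, *r* = 0: Var = (4/42) × 0.25 = 0.0238; standard error 0.154; noncentrality 0.21/0.154 = 1.36; power 0.26.

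| Teachers per school | ICC | *r* = 0 | *r* = 0.5 | *r* = 0.7 |
|---|---|---|---|---|
| 2 | 0 | 0.16 | 0.19 | 0.26 |
| 2 | 0.2 | 0.14 | 0.17 | 0.23 |
| 4 | 0 | 0.26 | 0.34 | 0.46 |
| 4 | 0.1 | 0.21 | 0.27 | 0.37 |
| 4 | 0.2 | 0.18 | 0.23 | 0.31 |
| 8 | 0 | 0.47 | 0.58 | 0.75 |
| 8 | 0.2 | 0.23 | 0.29 | 0.40 |

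A normal approximation gives nearly the same at four per school (0.19 to 0.48). A one-sided test there would give 0.29 to 0.60. At ICC 0, reaching 0.80 takes 18 teachers per school with *r* = 0, 14 with *r* = 0.5 and 10 with *r* = 0.7.

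**Detectable effect at 0.80 power, four per school** (normal approximation, 2.80 × √Var):

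- Smallest (ICC 0, *r* = 0.7): 2.80 × √0.0121 = 0.31 SD.
- ICC 0, *r* = 0: 2.80 × √0.0238 = 0.43 SD.
- Largest (ICC 0.2, *r* = 0): 2.80 × √0.0381 = 0.55 SD.

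**Sensitivity to the metric.** If 0.21 is Cohen's *f*, then *d* = 2 × 0.21 = 0.42. Power at four per school becomes 0.56 (ICC 0.2, *r* = 0) to 0.96 (ICC 0, *r* = 0.7), with 0.76 at ICC 0 and *r* = 0.

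**The case against.** The strongest reply is that a sample size is ordinarily justified for the primary outcomes, all of which are child-reported here. Civic skills is secondary, and teacher attitudes sits under Moderators in Table 1. On that view, low power for them is expected and no error has been made. The first part stands: low power on these outcomes is not a fault in itself. However, the sentence does not say it covers primary outcomes only, and by including moderators it already goes beyond them.

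Two further points also stand and limit the size of the concern:

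- The effect metric is unstated. Read as Cohen's *f*, the shortfall shrinks and in the favourable cases disappears.
- A class rating may have a smaller SD than a child score, so a child-level shift of 0.21 can be larger in class SD units. As an illustration with every value assumed, take a class ICC of 0.10, 25 children per class and a perfectly reliable rating. The class-mean SD is √(0.10 + 0.90/25) = 0.37, so *d* = 0.21/0.37 = 0.57 and power is about 0.95 with 168 independent teachers (42 × 4). At rating reliability 0.5 it is about 0.72, and at 0.25 about 0.44. This argument applies to civic skills but not to teacher attitudes, which are the teacher's own.

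A reader might infer that power for civic skills is known to be 0.2 to 0.5. The documents do not support that, because the teacher count, ICC, T1 correlation and metric are all assumptions. A reader might also infer that the trial plans to treat a null teacher result as no effect. No section says so; the Background warns that non-significant results may reflect poor implementation, and focus groups are planned to help interpret effects.

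**Conclusion.** The point holds as one about the scope of a claim. The protocol states 0.80 power at 0.21 for effectiveness and moderators without restriction, and two of its expected effects rest on teachers alone. If 0.21 is a standardised mean difference in the teacher score, power is about 0.14 to 0.75 over 2 to 8 teachers per school, ICC 0 to 0.2 and T1 correlation 0 to 0.7, and 0.18 to 0.46 at four per school. It stays below 0.80 throughout that range. Only beyond it does 0.80 come within reach: eight teachers per school, ICC 0 and a T1 correlation of 0.8 give 0.88.

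It would be too strong to conclude that the sample size was miscalculated, that 42 schools are too few for the primary outcomes, or that secondary outcomes must reach 0.80. The documents do not show any of these. The matter should be corrected, but it does not threaten the main analysis.

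**What to change.** In Study sample, limit the 0.80/0.21 sentence to the child-reported outcomes, provided the sponsor confirms these are what it was calculated for. Name the effect metric, sidedness, children per school and ICC behind it, and say that it does not extend to the outcomes measured in teachers only. Since 0.80 could not be confirmed even for the child outcomes, the revised sentence should rest on the sponsor's own calculation and not simply be repeated with a narrower scope.

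For civic skills and teacher attitudes, add a detectable effect based on the number of teachers actually expected, labelled as assumption-based (about 0.3 to 0.55 SD at four per school). State that both will be reported as estimates with confidence intervals, adjusted for the T1 score, and that a non-significant result will not be taken as adequately powered evidence of no effect. The assumed teacher count and power range used here should not be written in as facts.

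The cost is a few sentences and a less favourable stated power for these outcomes. No additional schools, participants or data are needed.
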